#### Clinical success

Venous Clinical Severity Score (VCSS) and/or Clinical Etiology Anatomy Pathophysiology classification (CEAP) Clinical score improvement of ≥1 point compared with baseline, assessed at 1 week, 1, 6, 12, 24 and 60 month(s) follow-up. Also, the overall changes in VCSS and CEAP Clinical score will be assessed during these follow-up moments.

#### Aesthetic result

Changes in aesthetic results are assessed using the aesthetic Numeric Analogue Scale ranging from 0 (unsatisfied) to 10 (very satisfied), at 1 week, 1, 6, 12, 24 and 60 month(s) follow-up and compared with baseline.

#### Disease-specific QoL

Changes in QoL are assessed using the VEINES-QOL/Sym (VEnous INsufficiency Epidemiological and Economic Study on Quality of Life/Symptoms) questionnaire,^27^ at 1 week, 1, 6, 12, 24 and 60 month(s) follow-up and compared with baseline.

#### Reinterventions

A reintervention is defined as a secondary treatment of the GSV in patients with anatomical failure after Flebogrif or EVLA treatment and assessed at 1 week, 1, 6, 12, 24 and 60 month(s) follow-up.

#### AASV reflux and neovascularisation

Ipsilateral reflux in the AASV and/or the occurrence of neovascularisation from the groin is assessed at 1, 6, 12, 24 and 60 month(s) follow-up.

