### Eligibility criteria

Patients are eligible for inclusion if they fulfil the following criteria:

Age 18–80 years.Unilateral symptomatic primary GSV and saphenofemoral junction (SFJ) incompetence.GSV diameter ≥4 and ≤12 mm.Intrafascial GSV length ≥15 cm.

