### Exclusion criteria

Bilateral endovenous thermal/MOCA treatment of the GSV.Simultaneous ipsilateral endovenous thermal/MOCA treatment of additional veins.C6 varicose veins.Previous ipsilateral GSV or anterior accessory saphenous vein (AASV) treatment.Superficial thrombophlebitis or deep venous thrombosis (DVT) in the last 6 months.Occlusion of deep venous system.Coagulation disorders or increased risk of thromboembolism.Use of direct oral anticoagulants or vitamin K antagonists.Pregnancy or lactation.Immobilisation.Cognitive impairment or language barrier.Allergy or contraindication to polidocanol.Severe renal or liver insufficiency.

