### Other measurements

Before treatment: gender (female or male); age; medical history (occurrence of migraine, asthma or chronic obstructive pulmonary disease, treatment of other leg vein(s)); use of platelet aggregate inhibitors; treatment side (right or left); baseline general pain score (assessed using an 11-point NRS ranging from 0 (no pain) to 10 (worst pain imaginable)); the presence of an (in)sufficient AASV and its confluence anatomy; GSV diameter (SFJ and mid-thigh) and length.During treatment: treated vein length; power in watts and total joules (EVLA); the amount of polidocanol foam used (Flebogrif); performance of concomitant phlebectomy of side branches.1 week, 1, 6, 12, 24 and 60 month(s) follow-up: treatment of side branches (phlebectomy and/or sclerotherapy (foam vs liquid, amount and percentage of polidocanol used)).

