#### Secondary outcome analysis

Categorical variables (technical success, safety, anatomical success, complications, clinical success, reinterventions, AASV reflux and neovascularisation) will be described as numbers with percentages. Between-group differences will be analysed using the χ^2^ test or the Fisher’s exact test where appropriate.

Continuous variables that are single measurements (operation time, intraprocedural and postprocedural pain scores) will be described as means with an SD in the case of normally distributed data and as medians with an IQR in the case of a non-normal distribution. Between-group differences will be analysed using the independent samples t-test or the Mann-Whitney U test depending on the data distribution.

Continuous variables that are measured at several moments (VCSS, CEAP Clinical score, aesthetic result and VEINES-QOL/Sym) will be described as means with an SD in the case of normally distributed data and as medians with an IQR in the case of a non-normal distribution. Between-group differences and change over time will be analysed using a linear mixed model. This type of analysis handles missing data well, making imputation unnecessary.

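### The AASV reflux outcome counts reflux present before treatment together with new reflux, so its rates cannot be read as new disease and any difference between arms is diluted

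*Protocol article*

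**What the plan says.** All references are to the protocol article.

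- **AASV reflux and neovascularisation** (secondary outcomes): "Ipsilateral reflux in the AASV and/or the occurrence of neovascularisation from the groin is assessed" at five visits, from 1 to 60 months. The AASV part is not restricted to new reflux and is not referred to baseline. The neighbouring outcomes of clinical success, aesthetic result and quality of life are each compared with baseline.
- **Eligibility criteria**: the condition on venous disease is "Unilateral symptomatic primary GSV and saphenofemoral junction (SFJ) incompetence". No condition is set on the AASV.
- **Exclusion criteria**: two entries touch the AASV. One is "Previous ipsilateral GSV or anterior accessory saphenous vein (AASV) treatment" and the other is "Simultaneous ipsilateral endovenous thermal/MOCA treatment of additional veins". Neither excludes an AASV that refluxes and is left untreated.
- **Other measurements**, before treatment: "the presence of an (in)sufficient AASV and its confluence anatomy". Table 1 also places duplex ultrasound (DUS) at screening, and its footnote lists AASV reflux among the purposes of DUS.
- **Secondary outcome analysis**: the categorical outcomes, including "reinterventions, AASV reflux and neovascularisation) will be described as numbers with percentages". The test is then stated: "Between-group differences will be analysed using the χ^2^ test or the Fisher’s exact test where appropriate". Baseline AASV status plays no part in it.

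**The concern.** Reflux that existed before randomisation cannot have been caused by either technique. If it is still there at a visit, the outcome as worded counts it.

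Two things follow. The percentage in each arm mixes prevalent with incident disease, so a reader cannot tell how often AASV reflux developed after treatment. In addition, the prevalent cases add roughly equal numbers of events to both arms. That pulls the risk ratio towards 1, shrinks the risk difference somewhat and adds variance, so a real difference in new reflux is harder to detect.

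**Working it through.** **The plan's own figure.** The only calculated figure is the primary sample size, which is not in dispute. With success of 95% and 93%, a margin of 10 points, one-sided 2.5% and 80% power:

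n per arm = (1.960 + 0.842)² × (0.95×0.05 + 0.93×0.07) / (0.10 − 0.02)² = 138.1, rounded up to 139, so 278 in total. Allowing for 10% loss, 139 / 0.9 = 154.4, so 155 per arm and 310 in total. This agrees with the article. It supplies the 139 evaluable per arm used below.

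**Inputs that are assumptions.** The documents give no AASV rates. Assumed are:
- new reflux of 5% in one arm and 15% in the other, among patients competent at baseline;
- baseline AASV incompetence b of 5%, 10% or 20% in both arms;
- a share s of that reflux persisting, with s = 1 first and s = 0.5 as a check.

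**Formulae.**
- Observed rate in an arm with new-reflux rate q: p = b·s + (1 − b)·q.
- Two-sided 5% power: Φ[(|p₁ − p₀| − 1.96·SE₀) / SE₁], where SE₀ = √(2p̄(1 − p̄)/n) and SE₁ = √((p₀(1 − p₀) + p₁(1 − p₁))/n).
- Any reflux uses n = 139. New reflux in patients at risk uses n = 139(1 − b), with rates of 5% v 15%.

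**Worked case, b = 10%, s = 1.** p₀ = 0.10 + 0.90×0.05 = 0.145 and p₁ = 0.10 + 0.90×0.15 = 0.235. The difference is 0.090 and the ratio 0.235/0.145 = 1.62. SE₀ = 0.0471 and SE₁ = 0.0467, so power = Φ[(0.090 − 0.0922)/0.0467] = 48%. In patients at risk, n = 125.1, SE₀ = 0.0379 and SE₁ = 0.0374, so power = Φ[(0.100 − 0.0743)/0.0374] = 75%. Pre-existing cases make up 0.10/0.145 = 69% of events in the lower arm and 0.10/0.235 = 43% in the higher.

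**Full persistence (s = 1).**

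| Baseline prevalence | Observed rates | Difference (points) | Risk ratio | Power, any reflux | Power, new reflux at risk |
|---|---|---|---|---|---|
| 0% | 5.0% v 15.0% | 10.0 | 3.00 | 80% | 80% |
| 5% | 9.75% v 19.25% | 9.5 | 1.97 | 61% | 78% |
| 10% | 14.5% v 23.5% | 9.0 | 1.62 | 48% | 75% |
| 20% | 24.0% v 32.0% | 8.0 | 1.33 | 32% | 70% |

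**Half persisting (s = 0.5).** At b = 10%, the rates are 0.05 + 0.90×0.05 = 9.5% and 0.05 + 0.90×0.15 = 18.5%. The difference is still 9.0 points, the ratio is 1.95 and power is 58%. At b = 5% the ratio is 2.31 and power 69%. At b = 20% they are 1.57 and 41%.

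**Chance imbalance at baseline.** The SD of the between-arm difference in prevalence is √(2b(1 − b)/139). At b = 10% this is 3.6 points. It describes variation that the test's standard error already contains, and is not an additional error.

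**The case against.** The strongest reply is that a journal article condenses the full protocol. The outcome section says what is assessed at each visit, and which patients form the denominator could be settled in the analysis plan, since baseline AASV status is collected. Part of this stands: an analysis plan that is not shown may use that status. But the article does more than leave a gap. It names AASV reflux as the outcome and fixes an unadjusted test for it, and followed as written these score pre-existing reflux as an event. The section on other outcome analysis would at most display a baseline imbalance. It would not remove prevalent cases from the outcome.

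Several stronger readings are tempting, and the documents do not support them.

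- *The comparison is biased, or a chance imbalance would pass for a treatment effect.* Randomisation balances baseline AASV reflux on average. Chance imbalance is part of the sampling error of the test, and the type I error rate stays nominal.
- *Every patient with baseline AASV reflux scores positive at every visit.* This assumes full persistence. The article allows phlebectomy of side branches in the same session and sclerotherapy of them at follow-up. It does not say whether an incompetent AASV would be handled that way or would resolve. The exclusion of simultaneous treatment of additional veins probably also removes some of these patients.
- *New reflux is hidden.* On the absolute scale the loss is modest, from 10 points to 9.5 to 8.0. The risk ratio and power suffer more.
- *The outcome exists to compare groin recurrence after tip positions of 1 cm and 0.5 cm below the SFJ.* The article describes these positions but never states that purpose.

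It is also fair to say that the trial is sized only for the primary outcome, and that 139 per arm is its 12-month figure, applied here to an outcome followed to 60 months.

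**Conclusion.** The point holds as a matter of definition. The outcome is any ipsilateral AASV reflux, an untreated incompetent AASV does not bar enrolment, and the stated test ignores the recorded baseline status. The reported rates would therefore not be rates of new reflux, and any true difference in new reflux would be diluted.

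The size rests wholly on assumed rates. With full persistence, moving from 5% to 20% prevalence lowers the risk ratio from 1.97 to 1.33 against a true 3.0, and power from about 61% to 32%. Restricting to patients at risk gives 78% to 70%. With half persisting at 10% prevalence the ratio is about 1.95 and power about 58%. If few enrolled patients have an incompetent AASV, the effect is small.

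This is a loss of precision and interpretability in one secondary outcome. It leaves the primary non-inferiority conclusion untouched, and it should be corrected because the correction is cheap.

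**What to change.** - Define the outcome as new AASV reflux: reflux at a follow-up visit in a patient whose AASV was absent or competent on the baseline DUS.
- Compare the arms within that group. Because it is defined by a pre-treatment finding, the randomised comparison is preserved.
- List patients with an incompetent AASV at baseline separately by arm, as persisting or resolved at each visit.
- Report neovascularisation from the groin as its own outcome in all patients, rather than joined to AASV reflux.

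The cost is a few lines of wording, best settled before the outcome data are analysed. The baseline status is already among the planned measurements, so no visit, patient or examination is added. The downside is a slightly smaller denominator for the AASV outcome: at 10% prevalence, about 125 instead of 139 per arm (139 × 0.90 = 125.1). Under the assumed rates this loses less power than the dilution does.

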### Other measurements

Before treatment: gender (female or male); age; medical history (occurrence of migraine, asthma or chronic obstructive pulmonary disease, treatment of other leg vein(s)); use of platelet aggregate inhibitors; treatment side (right or left); baseline general pain score (assessed using an 11-point NRS ranging from 0 (no pain) to 10 (worst pain imaginable)); the presence of an (in)sufficient AASV and its confluence anatomy; GSV diameter (SFJ and mid-thigh) and length.During treatment: treated vein length; power in watts and total joules (EVLA); the amount of polidocanol foam used (Flebogrif); performance of concomitant phlebectomy of side branches.1 week, 1, 6, 12, 24 and 60 month(s) follow-up: treatment of side branches (phlebectomy and/or sclerotherapy (foam vs liquid, amount and percentage of polidocanol used)).

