#### Anatomical success

The calculation is based on the hypothesis that MOCA using Flebogrif will have no inferior anatomical success 12 months after treatment, compared with EVLA. The anatomical success rate in the EVLA group is expected to be 95%.^22^,^25^ The anatomical success rate in the Flebogrif group is expected to be 93%.^18^,^20^ A non-inferiority margin of −10% is applied. This margin is based on the anatomical success rate of 85% after MOCA using Clarivein.^14 25 26^ Taking into account a power of 80% and a significance level of 2.5% (one-sided test on the lower level of the 95% CI of the expected difference), 278 patients will be needed (https://www.sealedenvelope.com/power/binary-noninferior/). Corrected for 10% lost to follow-up, 155 patients need to be included in each treatment group. The total study population will consist of 310 patients.

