### Study treatment

#### Intervention (Flebogrif) group

The included patients randomised to the intervention group will receive treatment with Flebogrif. The Flebogrif device is used to induce a combination of mechanical and chemical damage to the vein wall. The Flebogrif device is equipped with five retractable cutting/scratching elements that cause mechanical damage. The simultaneous, controlled administration of a foam sclerosant, results in chemical damage and obliteration of superficial venous trunks. No tumescent anaesthesia, sedation or antibiotics are required. The surgeons are experienced in the performance of endovascular procedures within the superficial venous system, with particular consideration of the specific nature and methodology of mechanochemical procedures. Prior to treatment, the GSV is marked using ultrasound. The patient is placed in supine position. Standard agents for disinfecting the operating field are used for skin desinfection. Thereafter, the leg is covered with sterile surgical drapes. Venipuncture is performed under ultrasound guidance with a 18G needle. A 0.035” guidewire is introduced through the 18G needle and placed at the level of the connection with the femoral vein (SFJ). The vascular sheath is introduced over the guidewire. After flushing the kit elements, the Flebogrif catheter, with a length of 60 cm, is inserted over the guidewire. The the working part of the tip is positioned at the predefined point, that is, 1 cm below the SFJ. Before releasing the cutting elements of the Flebogrif, the position of the catheter is checked. The cutting elements of the Flebogrif are fixated by clamping the clamping nut (2–3 cm per seconds). If the vein has a diameter of 8 mm or larger, two cutting passages will be performed over the entire length. The core part of the procedure consists of a steady withdrawal of the Flebogrif at a fixed speed, with concomitant injection of the sclerosant foam (3% polidocanol (EasyFoam), 2 mg/kg, 1 on 4 air). During foam injection, the groin is continuously compressed using the ultrasound head. The maximum amount of foam used will be 10 mL (50 cm). After the catheter is removed, manual pressure is applied to the area of the venipuncture. A detailed description of the Flebogrif design, enabling the correct use of the catheter as intended by the manufacturer, is contained in the operating instructions. After treatment, the deep venous system is checked using duplex ultrasound (DUS). If deemed necessary, additional phlebectomy of side branches is performed during the same session. A whole leg compression stocking (20–30 mm Hg) is applied continuously for the first 24 hours and continiued during the day for 1 week. Patients may resume normal activities immediately after the procedure but are given the advice to avoid peak pressure during the first week. If deemed necessary, additional sclerotherapy of side branches is performed during one of the follow-up visits. If additional sclerotherapy is performed, leg compression will be continued for 1 week.

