
#### Control (EVLA) group

The included patients randomised to the control group will receive treatment with EVLA. Prior to treatment, the GSV is marked using ultrasound. The patient is placed in supine position. Standard agents for disinfecting the operating field are used for skin desinfection. Thereafter, the leg is covered with sterile surgical drapes. Venipuncture is performed under ultrasound guidance with a 18G needle. A 6 F 11 cm sheet is introduced and followed by the introduction and positioning of the tip of the 1470 nm 2ring radial fibre (ELVeS Radial; Biolitec, Austria) 0.5 cm below the SFJ. Perivenous tumescent anaesthesia is administered using lidocaine 0.05% cold saline (5°C–10°C) and a roller pump (Nouvag Dispenser DP20). After administration of the tumescent fluid, the location of the tip of the laser fibre is checked. Laser treatment is performed using a continuous mode with a power of 10–12 watts. By slowly withdrawing the fibre, a targeted energy dose is delivered that is determined by the diameter of the GSV (approximately 80 J/cm). This process is repeated until the entire incompetent vein is ablated. After treatment, the deep venous system is checked using DUS. If deemed necessary, additional phlebectomy of side branches is performed during the same session. A whole leg compression stocking (20–30 mm Hg) is applied continuously for the first 24 hours and continued during the day for 1 week. Patients may resume normal activities immediately after the procedure but are given the advice to avoid peak pressure during the first week. If deemed necessary, additional sclerotherapy of side branches is performed during one of the follow-up visits. If additional sclerotherapy is performed, leg compression will be continued for 1 week.

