#### Primary outcome analysis

Anatomical success at 12 months of follow-up is a dichotomous variable and will be described as numbers with percentages. The difference between the two groups will be presented as a percentage with a 95% CI. If the lower limit of this CI does not exceed the non-inferiority margin of −10%, the intervention will be considered to be non-inferior. A second analysis will be performed in which data from the last follow-up visit before a reintervention will be used in patients undergoing a reintervention of the GSV after failure of primary treatment.

These analyses will be performed for both the ITT and the PP population. Patients with missing data on the primary outcome parameters will be excluded from analyses.

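### The valid crude primary comparison makes no use of GSV diameter, already recorded at baseline; pre-specified adjustment would be a cheap improvement with a small, uncertain gain

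*Protocol article*

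**What the plan says.** Under Primary outcome analysis in the protocol article, the endpoint is binary ("Anatomical success at 12 months of follow-up is a dichotomous variable and will be described as numbers with percentages") and the comparison is fixed as follows: "The difference between the two groups will be presented as a percentage with a 95% CI". The lower limit is then set against the margin of −10%. No covariate and no stratification factor is mentioned. The only regression model in the analysis plan is a linear mixed model, for repeated continuous secondary outcomes.

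Diameter appears in several other places:
- Eligibility criteria: veins of 4 to 12 mm are admitted.
- Other measurements: the list of items recorded before treatment includes "GSV diameter (SFJ and mid-thigh) and length".
- Intervention (Flebogrif) group: "If the vein has a diameter of 8 mm or larger, two cutting passages will be performed over the entire length".
- Control (EVLA) group: "a targeted energy dose is delivered that is determined by the diameter of the GSV".
- Randomisation and blinding: allocation is 1:1, stratified on surgeon (seven) and not on diameter.

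**The concern.** A baseline variable that spans a threefold range and steers treatment in both arms is a natural candidate to be prognostic for closure. If it is, a crude comparison leaves some explainable variation in the standard error. The point estimate also moves with any chance imbalance in diameter, which the stratification does not control.

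The trial has little room. At 139 per arm with 7 EVLA failures, about 10 Flebogrif failures are expected, and the Wald interval stops supporting non-inferiority between 12 and 13. The data for adjustment are already being collected, so the question is how much adjustment would buy.

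**Working it through.** **Inputs from the protocol article.** Expected success is 95% (EVLA) and 93% (Flebogrif). On the margin: "A non-inferiority margin of −10% is applied". Alpha is 2.5% one-sided and power 80%. The target is 278 evaluable patients, raised to 310 for 10% loss.

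**Assumed, not in the documents.** Diameter is normal with mean 6.5 mm and SD 1.8 mm, truncated to 4–12 mm. The log odds of failure are linear in diameter, with a range of odds ratios.

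**Step 1: reproduce the plan's figure.**
- n per arm = (1.96 + 0.8416)² × (0.95×0.05 + 0.93×0.07) / (0.10 − 0.02)² = 7.849 × 0.1126 / 0.0064 = 138.1, so 139 per arm and 278 in total.
- 278 / 0.9 = 308.9, which becomes 310 in equal arms.
- SE = √(0.1126/139) = 0.02846, so the 95% half-width is 5.58 points.
- Power = Φ(0.08/0.02846 − 1.96) = Φ(0.851) = 80.3%.

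The sample size therefore already assumes an unadjusted comparison.

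**Step 2: slack (Wald CI, 139 per arm, 7 EVLA failures).**
- 12 Flebogrif failures: difference −3.60 points, lower limit −9.51 (passes).
- 13 Flebogrif failures: difference −4.32 points, lower limit −10.37 (fails).

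**Step 3: precision from adjustment.** Trials were simulated at 139 per arm. The variance of the standardised logistic risk difference was divided by that of the crude difference to give a ratio r. Power follows as Φ(0.08/(0.02846√r) − 1.96).

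| Odds ratio of failure per mm | Odds ratio across 4–12 mm (8th power) | r | Power |
|---|---|---|---|
| 1.0 | 1 | 1.00 | 80.3% |
| 1.2 | 4.3 | 1.00 | 80.3% |
| 1.4 | 14.8 | 0.985 | 80.8% |
| 1.6 | 43 | 0.958 | 81.9% |
| 2.0 | 256 | 0.925 | 83.2% |

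At 1.6 per mm the half-width falls from 5.58 to 5.58 × √0.958 = 5.46 points. That is worth about 278 × 0.042 ≈ 12 patients.

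**Step 4: cross-check.** A large-sample formula gives the variance per arm as {2E[p_C(1−p_C)] + 2E[p_T(1−p_T)] + Var(p_T − p_C)}/2, where p is the failure probability given diameter. The variance reduction is 1.1% at an odds ratio of 1.5 per SD, 3.5% at 2.0 and 9.5% at 3.0. Power is 80.7%, 81.6% and 84.0%. An odds ratio of 2.0 per SD is about 2^(1/1.8) = 1.5 per mm, a little more once truncation shrinks the SD. The two methods agree in size.

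**Step 5: chance imbalance.**
- The SE of the difference in mean diameter is 1.8 × √(2/139) = 0.216 mm, so an imbalance of 0.3 mm is 1.39 SE. One at least that large, in either direction, occurs in about 16% of trials.
- At an assumed odds ratio of 1.5 per mm, the crude difference shifts by about 0.06 × 0.94 × ln 1.5 × 0.3 = 0.0069, or 0.7 points. One failure in 139 is 0.72 points.

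**Step 6: does adjustment do harm?** In the simulations it cost no power. The rate of false non-inferiority claims was about 3% with either analysis. Non-convergence, or an arm with no failures, occurred in at most about 0.2% of trials.

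**The case against.** The strongest reply is that nothing here is wrong. The crude risk difference is what the trial was sized for. Randomisation protects its type I error, and its interval already covers chance imbalance. All of that stands. The 0.7-point shift is ordinary sampling error inside a half-width of 5.58 points, and precision that the sample size never counted on cannot be called lost.

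A reader might infer from the two treatment sections that the protocol regards diameter as a driver of closure. The documents do not support this. They tailor treatment to diameter, which is a different statement, and tailoring could weaken any link with the outcome. The larger gains also need steep gradients: an odds ratio of 2.0 per mm is 256-fold across the admitted range.

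Nor is adjustment free. About 139×0.05 + 139×0.07 = 16.7 failures are expected. Seven surgeons, arm and diameter would take eight coefficients besides the intercept, about two failures each. Two diameters are recorded, and the plan does not say which one governs eligibility or treatment. A switch of method without a stated trigger would add discretion to an analysis that is now simple.

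Finally, a statistical analysis plan that is not shown may already specify adjustment. That limits confidence, although the article does state a particular primary comparison.

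**Conclusion.** The planned analysis is valid and adequately powered on its own assumptions. What remains is a modest missed opportunity: a baseline variable that is recorded, steers treatment and is not balanced by stratification goes unused. For assumed odds ratios of 1.2 to 1.6 per mm, adjustment would reduce the variance by about 0–4% and raise power from 80.3% to at most about 82%. With no association, essentially nothing changes either way. These figures rest on an assumed diameter distribution and an assumed prognostic strength, neither of which the documents give. It is an optional improvement, held with low confidence as to its value.

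**What to change.** Before outcome data are compared by arm, record the following in the analysis plan:
- Estimate the marginal difference in 12-month success by standardisation from a logistic model with arm and one named baseline diameter (SFJ or mid-thigh), continuous and linear. Use a robust 95% CI against −10%. This keeps the risk-difference scale on which the margin is defined.
- Report the crude difference and its CI beside it.
- Fall back to the crude difference if the model does not converge or an arm has no failures, with no other switch of method.
- State how surgeon, the actual stratification factor, is handled given about 17 expected failures.

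The cost is a little more modelling and a choice between the two recorded diameters. Sample size, visits and treatment are unaffected. The timing matters because the trial is open-label, and adjustment chosen after an imbalance has been seen would look data-driven.
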